### Statistical analysis

2.6

Descriptive statistics for all relevant variables, such as changes in motivation, upper limb function and/or attention/concentration skills, will be calculated (means, standard deviations, etc.). Assumptions of all statistical analyses will be checked, and appropriate measures will be taken in case of violations (e.g., transformations, nonparametric testing, or bootstrapping). Effect sizes will be calculated for each effect (e.g., Cohen's *d*). Statistical tests will be performed with an alpha level of p ≤ .05 to determine statistical significance of results. Because of the randomised design, possible bias introduced by missing data will be controlled for using an intention-to-treat (ITT) analysis performed on all subjects who complete the baseline measurements, to assess whether data is missing randomly. If so, these may be completed with imputed data. Given the relatively small sample size of the study, this allows for a per-protocol analysis to also be conducted on datasets with missing data points, and the results from the ITT analysis will be verified on subjects who completed the entire study protocol, including all measurements (e.g. Ref. [57]). If needed, data analysis procedures with more robustness for missing data will be utilised (i.e., multilevel models). The self-reported motivation for sessions attended for other interventions offered at the rehabilitation centre will be recorded and compared between subjects as well as between sequences (AB/BA). Carry-over effects due to the cross-over design will be assessed by examining a treatment-by-period interaction. A significant difference between the two intervention or control phases of the AB/BA sequence, will result in significant treatment-by-period interaction indicating a carry-over effect (Lim & In, 2021). In case a significant carry-over effect is found, we will control for this in the analysis.

Other aspects that may be used as covariates in post-hoc analyses to interpret results at the group level are individual differences in diagnostic intake measures, age, and qualitative clinical observations or situations that may affect motivational states.

The primary analysis concerns the change in motivation scores (BMQ-S) between the control and intervention period, controlling for the order of conditions. Additionally, a correlation between changes in motivation with changes in functional outcome measures (motor, cognition, mood) will be calculated. For our secondary analysis, changes in functional measures will be compared between control and intervention periods to assess effectiveness of NMT. As exploratory analyses, correlations between functional improvements and possible predictors such as musical engagement, optimism, personality traits and expectations of NMT will be calculated. Finally, self-reported motivation for other rehabilitation specialisms will be compared between the intervention and control period. Participants will be included if they have completed at least 6 sessions of Music Therapy.

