#### Sample size calculation/power analysis

2.3.1

In a previous study, 40 stroke patients in the sub-acute phase were allocated to either 20 30-min sessions of music-supported therapy (N = 20; 4 withdrew/excluded; 16 in final analysis) or twenty additional sessions of conventional therapy (N = 20; 2 withdrew/excluded; 18 in final analysis) [35]. The study found a significant correlation (r = 0.562, p = 0.024) between patients’ intrinsic motivation to engage in musical activities as measured by the Barcelona Music Reward Questionnaire (BMRQ, [36]) at baseline and improvement of upper-limb function as measured by the Action Research Arm Test (ARAT, [37]) at 3 months, which was not found in the comparator of occupational/physical therapy (r = −0.305, p < 0.21), with a significant difference between correlations (z = 2.4, p < 0.05). Using Gpower 3 analysis, we estimated that 18 participants are needed to observe a similar effect size for a sufficiently powered study (α = 0.05 and (1-β) = 0.8; ρ H1 = 0.56). This indicates that 20 participants completing the entire protocol would be required to observe an effect of motivation in music therapy, with a hypothesised attrition/missing data rate of 10–20 %. This sample size is similar to the number of participants used in studies showing an effect for our secondary objectives, ranging from 14 to 20 participants, on the effects of music therapy on motor function [38], cognition, and psychological wellbeing [39]. Recruitment will continue until 20 participants have completed the protocol.

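### Section 2.6 relies on an ITT analysis to judge whether data are missing at random and lets that judgement open imputation, but neither ITT nor the observed data can establish it

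*Protocol article*

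**What the plan says.** The protocol article, section 2.6 (Statistical analysis), sets out a chain of steps for missing data:

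- Purpose: "possible bias introduced by missing data will be controlled for using an intention-to-treat (ITT) analysis".
- Population and use: this analysis is "performed on all subjects who complete the baseline measurements, to assess whether data is missing randomly".
- Consequence: "If so, these may be completed with imputed data".
- Per-protocol analysis: because the sample is small, "this allows for a per-protocol analysis to also be conducted on datasets with missing data points", and in the same sentence "the results from the ITT analysis will be verified on subjects who completed the entire study protocol, including all measurements".
- Fallback: "If needed, data analysis procedures with more robustness for missing data will be utilised (i.e., multilevel models"). No trigger for it is given.

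Three other places set who is analysed. Section 2.2 ties the primary analysis to completing at least 6 sessions, section 2.5.3 does the same for the final analyses, and the last sentence of section 2.6 repeats the restriction.

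Section 2.3.1 plans for 20 completers and a 10–20% rate of attrition or missing data. The primary analysis (section 2.6) is the change in BMQ-S between control and intervention periods, controlling for order.

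**The concern.** The rule gives ITT a job it cannot do. ITT is a choice of analysis set: everyone randomised, in the sequence assigned. It says nothing about why a value is absent, and it does not remove the bias from that absence. Observed data can give evidence against missing completely at random. They cannot show that data are missing at random rather than missing not at random, because the two differ only in how missingness depends on values nobody saw. The condition that opens imputation therefore cannot be established.

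This is a rule stated wrongly, not a detail left to a fuller plan. A later document would have to replace the sentence, not add to it.

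At stake is how the primary estimate is built. The introduction defines motivation partly as the drive to take part in therapy, and motivation is also the primary outcome, so a link between leaving the trial and the outcome is plausible on the protocol's own terms. A data-dependent judgement, with no stated criterion, would then choose between imputation and other handling after the data are seen.

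**Working it through.** The plan gives no figure for the performance of its missingness check, so there is none to reproduce. The check was sized from the plan's own numbers.

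**1. How many participants would have missing data.** Inputs from section 2.3.1: 20 completers, 10–20% attrition.
- 20/(1 − 0.10) = 22.2, so 23 enrolled and 3 missing.
- 20/(1 − 0.20) = 25, so 25 enrolled and 5 missing.
- If 20 is read as the total instead, 10–20% is 2 to 4 missing.

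The range used is 2 to 5.

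**2. Power of a plausible check.** The protocol names no test. Assumption: a t-test of one baseline score, dropouts against completers, two-sided at 0.05 (section 2.6 gives the 0.05 level but not the sidedness). With n₁ dropouts, n₂ = 20 completers and standardised difference d, the non-centrality is d × √(n₁n₂/(n₁+n₂)) on n₁+n₂−2 degrees of freedom. At d = 0.8:
- 2 dropouts: 0.8 × √(40/22) = 1.08, 20 df, power 18%.
- 3 dropouts: 0.8 × √(60/23) = 1.29, 21 df, power 23%.
- 4 dropouts: 0.8 × √(80/24) = 1.46, 22 df, power 29%.
- 5 dropouts: 0.8 × √(100/25) = 1.60, 23 df, power 34%.

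For 80% power the difference would have to be 2.19 SD with 2 dropouts and 1.47 SD with 5.

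A check of missingness by sequence does little better. Even if every missing participant fell in one sequence, Fisher's exact p would be 0.47 (2 of 20), 0.21 (3 of 22), 0.087 (4 of 20) and 0.037 (5 of 24).

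**3. What the check can see under non-random dropout.** In a simulation of 25 participants with the 5 worst outcomes missing, the same t-test on baseline rejected in 5.1% of trials when baseline and outcome were uncorrelated (its nominal level), 40% at correlation 0.5 and 75% at 0.7. In all three cases the completers' mean was off by about 0.34 SD. The check responds to the baseline–outcome correlation and not to the size of the bias. The 0.34 SD is the error in a single mean, not in the primary contrast, so step 4 is needed.

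**4. Effect on the within-subject contrast.** Assumptions: AB/BA design, 25 randomised, worst 5 lost, completers analysed, true effect 0.5 SD for everyone, intraclass correlation 0.6, contrast of the change over the NMT period with the change over the control period.
- Dropout driven by stable motivation, baseline score or TP3 score: mean estimate 0.50, unbiased.
- Dropout driven by TP2 score: mean estimate 0.42, a loss of 0.08 SD.
- Dropout driven by individual response: if responses vary with SD 0.5 (a further assumption) and the 5 weakest responders leave, the 0.34 SD shift from step 3 applies to the response itself, giving 0.34 × 0.5 = 0.17, so about 0.67 instead of 0.50.

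The bias can be nil, downward or upward, according to the mechanism.

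**5. The analysis sets side by side.** The ITT set is everyone with baseline measurements. Sections 2.2, 2.5.3 and 2.6 then limit the primary or final analysis to those with at least 6 sessions. Someone with baseline data who stops after fewer sessions is in the first set and outside the second, and the text does not say which set yields the primary estimate.

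**The case against.** The strongest reply is that this is loose drafting with limited consequences. Several parts of it stand.

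- A reader might infer that a failed check leaves only completers. The text does not say so. It offers multilevel models if needed and makes the completer analysis a verification of the ITT result.
- A reader might infer that imputation happens only if the check passes. That is the natural reading, but the wording is permissive: values may be imputed.
- The 18–34% rests on a t-test the protocol never names. Other checks, or missingness strongly tied to baseline, would do better, as the 75% in step 3 shows.
- A reader might infer that dropout among the poorly motivated must bias the primary result. It need not. Each participant is their own control, and step 4 shows the contrast intact when dropout follows stable or baseline motivation. Where dropout follows the TP2 score and that score was recorded, a multilevel model can use it.
- The two per-protocol phrases sit in one sentence and can be read together: where some data are missing, an analysis of full completers is run as well. This is unclear drafting, not a proven contradiction.
- A multilevel model fitted by likelihood also assumes missing at random.

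None of this makes the condition valid. The fallback has no trigger, and a completer analysis cannot reveal bias that comes from who completes. An assumption stated in advance and probed by a sensitivity analysis is also different from one treated as confirmed by a check that cannot confirm it.

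**Conclusion.** The point holds in limited form. Section 2.6 wrongly treats ITT as an assessment of the missingness mechanism and conditions imputation on a state that observed data cannot verify. That conclusion needs no calculation.

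The size is illustrative. Under the assumed t-test and the plan's own numbers, power to notice a 0.8 SD baseline difference is about 18–34%. The documents do not support saying that the primary estimate will be biased. In the examples it ranged from no bias, through 0.08 SD too small, to 0.17 SD too large on a true effect of 0.5 SD, depending on assumptions the protocol cannot settle in advance. The conflict between the ITT set and the six-session restriction is on the page and affects the same estimate. The change is worth making before data are seen. It does not call the design into question.

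**What to change.** In section 2.6:

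1. Delete the condition that data be judged missing at random before imputation, and stop describing ITT as the means of controlling missing-data bias.
2. Make the multilevel model already named there the primary analysis, fitted to all randomised participants with baseline data, using every available BMQ-S score from TP1 to TP3. State that it assumes missing at random.
3. Add one simple missing-not-at-random sensitivity analysis: shift the missing BMQ-S scores by a range of deltas fixed in advance. Let the delta differ between NMT and control periods, since an equal shift in both would largely cancel in the within-subject contrast.
4. Define the per-protocol set once, as supportive only. Reconcile it with the at-least-6-sessions wording in sections 2.2, 2.5.3 and 2.6, so that the restriction no longer governs the primary analysis while ITT is also claimed.

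The cost is analysis wording and a little extra analysis work. Recruitment, visits and measures do not change.

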## Abstract

Stroke is a highly disabling condition, for which music therapy is regularly used in rehabilitation. One possible mechanism for the effects of music therapy is the motivational aspect of music, for example regarding treatment adherence based on improved mood. In this study, changes in motivation related to Neurologic Music Therapy (NMT) techniques during rehabilitation in the subacute phase after stroke will be investigated. Using a randomised within-subjects cross-over design, the effects of two NMT techniques and related motivational indices will be investigated. Data will be collected at three timepoints: baseline (TP1), after being randomised into groups and receiving NMT or standard care (TP2), and then at a third time point after the cross-over and having received both conditions (TP3). This design allows to counteract order effects, time effects due to spontaneous and/or nonlinear recovery, as well as single-subject comparisons in a relatively heterogeneous sample. Twenty adult participants who have experienced a supratentorial ischaemic or haemorrhagic stroke and are experiencing upper-limb impairments and/or cognitive deficits will be included. Behavioural measures of motor function, cognition, and quality of life will be collected, along with self-reported indices of overall motivation. The study outcomes will have implications for the understanding of the underlying mechanisms of music therapy in stroke recovery, more specifically regarding the relevance of motivational states in neurorehabilitation.

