### Study design

2.2

The study will employ a within-subject cross-over design; as stroke patients are not a homogenous group, this design is adopted to control for expected within-subject variation. To account for variability in brain damage that is caused by stroke, each subject thus serves as their own control. The cross-over design will account for order effects, as participants will be randomised into either receiving the intervention or the control phase first (AB), and vice versa (BA), while also allowing for the assessment of the intervention effectiveness (as part of the secondary goal).

All subjects will receive two NMT techniques targeting both upper-limb movement and attention. The study aims for participants to receive 9 sessions of NMT over 3–6 weeks, however, participants who complete a minimum of 6 sessions will be included in the primary analysis. The frequency of clinical contacts will aim for an average of 2–3 sessions per week but will be adjusted to a patient's expected length of stay and ability, using a tailored approach. Dosage will depend on a participant's rehabilitation trajectory, as subacute patients generally are admitted for a minimum of ±6 and a maximum of 16 weeks.

Fig. 1 gives an overview of the design and procedures that the subjects will undergo within the course of the research, based on a rehabilitation trajectory of 8–10 weeks. When participants’ rehabilitation trajectory is shorter (6–8 weeks) or longer (12–16 weeks), then the intervals between baseline, mid-trial and final measures are adjusted accordingly.

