#### Randomisation, blinding, and treatment allocation

2.5.2

Participants will receive two conditions in a randomised order: a) music-therapy intervention, and b) control condition involving standard care. The randomisation sequence will be computer generated (allocation 1:1). Due to the nature of the intervention, the clinical setting, and since the music therapist providing the intervention is one of the researchers, blinding of the researchers and assessors is not possible. However, the data analyses will be carried out blinded to the treatment order i.e. adding a round of pseudonymisation and nondescript labelling of experimental versus control periods.

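### The stated sign of carry-over compares phases from opposite periods, so it measures recovery over time as well as, or instead of, carry-over

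*Protocol article*

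**What the plan says.** Three statements in the Statistical analysis section (2.6) follow one another. The test is named: "Carry-over effects due to the cross-over design will be assessed by examining a treatment-by-period interaction". It is then explained: "A significant difference between the two intervention or control phases of the AB/BA sequence, will result in significant treatment-by-period interaction indicating a carry-over effect". Finally a consequence is attached: "In case a significant carry-over effect is found, we will control for this in the analysis". The method of that control is not given. The significance level is set generally: "Statistical tests will be performed with an alpha level of p ≤ .05 to determine statistical significance of results".

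The Study design section (2.2) fixes the order of the phases: "participants will be randomised into either receiving the intervention or the control phase first (AB), and vice versa (BA)". The Abstract says of time effects: "This design allows to counteract order effects, time effects due to spontaneous and/or nonlinear recovery". The same section 2.6 defines the primary analysis on the change in BMQ-S between the control and intervention periods, controlling for order, and compares changes in the functional measures in the same way.

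**The concern.** The explanatory sentence equates two different quantities. Participants in AB have the intervention in period 1, and participants in BA have it in period 2. Comparing like phase with like phase across the sequences therefore also compares period 1 with period 2. Whatever makes change differ between the periods goes into that comparison, whether or not carry-over exists.

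In this trial such a difference is plausible. Patients are subacute, the protocol expects spontaneous and possibly nonlinear recovery, and section 2.2 lets the intervals between measurements vary with length of stay. An analyst who follows the sentence could label recovery as carry-over and then alter the primary and functional analyses because of it. The cross-over with period in the model already handles that nuisance without any pre-test.

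**Working it through.** The plan gives no figure for carry-over or for a period effect, so there is none to reproduce. The sample-size figure of 18 concerns a correlation and does not bear on this point.

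**Inputs from the protocol.** Twenty completers ("Recruitment will continue until 20 participants have completed the protocol") and equal allocation ("The randomisation sequence will be computer generated (allocation 1:1)") give about 10 per sequence. Alpha is 0.05, taken as two-sided because the sidedness is not stated. The outcome is change per period: TP2 − TP1 and TP3 − TP2.

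**Assumptions.** Each time point has SD 1, and all pairs of time points correlate 0.7. Mean change in period 1 exceeds that in period 2 by g = 0.3, 0.5 or 0.8 SD.

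**Step 1: what each comparison estimates.** Let π be the period effect (period 2 minus period 1), τ the treatment effect, and λ the carry-over into period 2 of AB.

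| | Period 1 | Period 2 |
|---|---|---|
| AB | τ | π + λ |
| BA | 0 | π + τ |

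- Intervention phases: (π + τ) − τ = π. There is no carry-over term.
- Control phases: (π + λ) − 0 = π + λ.
- Interaction (difference in participant totals): (τ + π + λ) − (0 + π + τ) = λ. There is no period term.

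A like-phase difference therefore does not imply the interaction.

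**Step 2: how often recovery alone is flagged.** Set λ = 0 and τ = 0. The SD of a change is √(2 × (1 − 0.7)) = √0.6 = 0.775. The standardised difference is g/0.775. With 10 against 10 the noncentrality is that value times √(10/2) = √5, and the two-sided t test has 18 degrees of freedom.

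| g (SD) | g/0.775 | Noncentrality | Intervention phases significant | Totals test |
|---|---|---|---|---|
| 0.3 | 0.387 | 0.866 | 13.0% | 5% |
| 0.5 | 0.645 | 1.443 | 27.7% | 5% |
| 0.8 | 1.033 | 2.309 | 58.9% | 5% |

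Simulation of 40,000 trials per setting agrees with these rates. If a significant result on either the intervention or the control phases counts, the rates are about 21%, 42% and 76%. In the same runs the period-adjusted treatment test stayed at 5%.

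**Step 3: what adjusting for carry-over leaves.** With λ free, the two period-2 cells serve to estimate π and λ. The treatment effect then comes from period 1 only: AB minus BA = τ, about 10 against 10.

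**Step 4: which carry-over matters for change scores.** The period-adjusted estimate is ½[(AB1 − AB2) − (BA1 − BA2)]. Take a true effect of 0.5 SD.

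- Gain fully kept: ½[(0.5 − 0) − (0 − 0.5)] = 0.50. There is no bias, and TP3 − TP1 is equal in the two sequences.
- Gain fully lost during the later control period: ½[(0.5 + 0.5) − (0 − 0.5)] = 0.75. The totals differ by 0.5 SD. At correlations of 0.5, 0.7 and 0.8 the SD of TP3 − TP1 is 1.000, 0.775 and 0.632, and the totals test detects the difference in about 19%, 28% and 39% of trials.

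**The case against.** The strongest reply is that the sentence before the faulty one names a valid test. If only a true treatment-by-period interaction is run, an additive period effect cancels and recovery is not flagged. That stands. A reader might infer that the trial will report recovery as carry-over, but the document supports only that it could if the explanatory sentence is followed. The two sentences can still give different answers on the same data, so one has to go.

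A reader might also infer a seriously inflated error rate, or that lasting learning would be an undetected carry-over. Neither holds for the planned change scores. Testing with the correct totals test and then falling back on period 1 has a simulated type I error of about 5.5–5.7%, close to nominal, and Step 4 shows that a lasting benefit does not bias the estimate.

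The fallback on period 1 is itself not stated. The protocol does not say how it would control for carry-over, so the effect on the primary result cannot be computed, and the analysis plan may give that detail.

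The sizes of g are assumptions. The protocol's statement on recovery concerns neurological and functional recovery, not self-reported motivation, and it does not say that recovery decelerates. With linear change over equal periods, the like-phase comparison of change scores would not be triggered. However, the protocol allows for nonlinear recovery and variable intervals, so this cannot be relied on.

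**Conclusion.** The point holds as an error in a stated rule. The intervention-phase comparison contains no carry-over, and the control-phase comparison mixes carry-over with the period effect. This is algebra and needs no assumed values. The false-flag rates of about 13%, 28% and 59% rest on 10 per sequence, correlation 0.7 and assumed period differences of 0.3, 0.5 and 0.8 SD in the outcome. The correct totals test stays at 5% throughout.

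The attached conditional adjustment is unspecified and lets the data choose the analysis. Any carry-over-adjusted estimate would rest essentially on period 1. The planned order-adjusted contrast of changes is not itself shown to be invalid. The carry-over that would bias it is fading of the NMT gain during a later control period, and a test with 10 per sequence detects even complete fading of a 0.5 SD effect in only about 19–39% of trials. A significance test is therefore a poor basis for choosing the analysis, even when computed correctly.

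**What to change.** 1. Delete the sentence that equates a like-phase difference with carry-over, and the sentence that makes an adjustment conditional on a significant result.
2. Fit one pre-specified model of the change scores with treatment and period as fixed effects, participant as a random effect, and sequence if wanted, whatever the interaction shows. Allow the two changes from one participant to be negatively correlated, for example through an unstructured two-by-two covariance, because both contain TP2.
3. Always report, as a sensitivity analysis, the period-1 comparison of TP2 between sequences adjusted for TP1. Carry-over cannot affect it.
4. If a carry-over estimate is shown, give it descriptively with its confidence interval as the between-sequence difference in TP3 minus TP1, and do not use it to choose the analysis.

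The cost is a change of wording and one extra model. No data collection changes. The sensitivity result will be less precise than the cross-over estimate, and the report should say so.
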